**Primary outcomes**							
Person with dementia: improvement in quality of life	QOL-AD	QOL-AD	QOL-AD	QOL-AD	QOL-AD	QOL-AD	QOL-AD
Carer/family members: improvement in well-being	CES	CES	CES	CES	CES	CES	CES
**Secondary outcomes**							
Person with dementia: reduced symptoms of depression	GDS 15		GDS 15			GDS 15	GDS 15
Person with dementia: increase in social activities	Interview/client records		Interview/client records	Interview/client records		Interview/client records	Interview/client records
Person with dementia: increase in social engagement	Interview/client records		Interview/client records	Interview/client records		Interview/client records	Interview/client records
Person with dementia: change in health service utilization	RUD		RUD	RUD		RUD	RUD
Person with dementia: delay in accessing permanent residential aged care services	Interview/client records		Interview/client records	Interview/client records		Interview/client records	Interview/client records
Carer/family members: reduction in depression/psychological distress	GHQ-12		GHQ-12			GHQ-12	GHQ-12
Carer/family members: increase in social engagement/ability to continue regular activities	Interview/client records		Interview/client records	Interview/client records		Interview/client records	Interview/client records

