### Trial Design

The evaluation of the “*Support for Life*” complex intervention will occur within a step-wedge cluster Randomized Controlled Trial (cRCT) involving multiple community health centers across three states over 3 years. Clusters are the community health centers, and approximately 10 centers in each state will participate in this study. Half of the centers (Group A) will be randomized to receive the intervention in year 1 and the other half in year 2 (Group B).

This “*Support for Life*” complex intervention proposes to trial a framework of a single service, highly flexible holistic approach to support for people with dementia and their families/carers. It will provide a platform to integrate current services and health care, provide emotional support, and enhance community and social engagement. Important principles are
Protecting the person with dementia and their rights to full citizenship regardless of their age, gender, and cultural background.Providing access to support where there is diminished decision-making capacity, retaining respect for the person with dementia but also the advocating for the rights of the family and caring unit.Improving access to palliation and “end of life care” in the setting of advanced or impaired decision-making, including with those who live alone.

This type of response builds on the strengths in a caring unit and addresses the needs of individual relationships. In line with “codesign” and “consumer directed care” (CDC) principles, the person with dementia, their family, and other members of the caring unit will actively design/influence what this service response will look like. Ongoing evaluation will allow for flexibility and change.

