### Outcomes

**Primary outcomes** (baseline, 3, 6, 12, 15, 18, and 24 months)*Person with dementia*
Improvement in quality of life (suitable for use by people with moderate to severe levels of dementia) (QOL-AD) (7)*Carer/family members*
Improvement in well-bein*g* of carer/family unit [Carer experience scale (CES)] (8, 9)**Secondary outcomes** (baseline, 6, 12, 18, and 24 months)*Person with dementia*
Reduction in symptoms of depression (GDS 15) (10)Increased attendance at social activities/services (staff/family/carer report/interviews)Increased engagement in social activities/services/ability to continue to participate in regular activities (staff/family/carer report/interviews)Change in health-care service utilization [client records/resource utilization in dementia (RUD) (11) health records]Delay in accessing permanent residential aged care services (client records/interviews)*Carer/family members*
Reduction in carer depression/psychological distress [General Health Questionnaire-12 (GHQ-12)] (12)Increase in social engagement and ability to continue regular activities (self report/interviews).

(See Table 1 for a full list of instruments).

**Table 1 T1:** **Outcome measures**.

	Baseline	3 months	6 months	12 months	15 months	18 months	24 months

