### Schedule of Events

At baseline, we will administer the primary and secondary measures to all participants. At 3, 6, 12, 15, 18, and 24 months, we will administer the primary measures. At 6, 12, 18, and 24 months, we also administer the secondary measures. All participants will follow this schedule of data collection regardless of group allocation. See Figure 1.

The intensive intervention phase at each cluster is shown in Figure 1. During this phase, the intervention will be actively promoted at the indicated clusters. The post-intervention phase is shown in light-blue, where participants can still access the intervention, but the intervention will no longer be actively promoted at those clusters.

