## Methods: Data Collection, Management, and Analysis

Primary and secondary data collection will occur at baseline and 3, 6, 12, 15, 18, and 24 months post-randomization (Figure 1). This will involve a face to face visit with a researcher. Participants will receive a telephone call and an information letter with study questions 10 to 14 days prior to the baseline and all follow-up visits. The telephone contact will be used to arrange a mutually suitable time and location for the face to face visit as well as provide information to participants about what will take place at the forthcoming visit. Participants will have the option to complete questionnaires prior to the visit or complete them during the researchers visit. Interviews will take place during the face to face visit and will be audio-taped prior to transcription and importation into the NVivo Qualitative Software to aid analysis. The researcher will be trained in quantitative and qualitative data collection methods and any relevant outcome measure assessments. They will also be experienced in communicating with people with dementia and their carers and families including collecting data from participant and proxy (carer/family member) when necessary.

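### Table 1 leaves GDS 15 and GHQ-12 blank at 12 months, contradicting three text sections; if the table were followed, both would keep only one wave against concurrent usual care

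*Protocol article*

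**What the plan says.** The protocol article gives the timing of the secondary measures in four places.

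- **Outcomes section.** The list of secondary outcomes, which names GDS 15 and GHQ-12, is headed "baseline, 6, 12, 18, and 24 months".
- **Schedule of Events.** "At 6, 12, 18, and 24 months, we also administer the secondary measures". Baseline is covered by the sentence before it. No instrument is excepted, and the schedule applies to both groups.
- **Methods: Data Collection, Management, and Analysis.** "Primary and secondary data collection will occur at baseline and 3, 6, 12, 15, 18, and 24 months post-randomization".
- **Table 1 ("Outcome measures").** The rows "Person with dementia: reduced symptoms of depression" and "Carer/family members: reduction in depression/psychological distress" are filled at baseline, 6, 18 and 24 months and are blank at 3, 12 and 15 months. The other five secondary rows, for example "Person with dementia: change in health service utilization", are filled at baseline, 6, 12, 18 and 24 months.

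Under Trial Design and Intervention, Group A centers start in year 1, and Group B centers stay on usual care in year 1 and start in year 2. The Hypotheses section states both depression/distress hypotheses as comparisons of the intervention group with the control group.

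**The concern.** The schedules cannot all be followed. The two instruments that Table 1 drops at 12 months are the ones that carry the depression hypothesis for people with dementia and the distress hypothesis for carers.

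Month 12 closes Group A's intensive year. On the year 1/year 2 wording it is also the last scheduled wave at which Group B is still on usual care. From 18 months both groups have access to the intervention. Without the 12-month wave, a randomised comparison with concurrent usual care exists only at 6 months, and Group B's crossover is bracketed only by the 6- and 18-month visits. A wave that was not collected cannot be recovered later.

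**Working it through.** **Step 1: is the blank real?** Table 1 has seven time columns: baseline, 3, 6, 12, 15, 18 and 24 months. Each of the two rows has a label and seven cells, so the gap is not a column shift. It appears in two separate rows, while five secondary rows in the same table are filled at 12 months. A text-extraction fault is unlikely.

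**Step 2: the four schedules side by side, for GDS 15 and GHQ-12.**

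| Source | 0 | 3 | 6 | 12 | 15 | 18 | 24 |
|---|---|---|---|---|---|---|---|
| Outcomes section | x | | x | x | | x | x |
| Schedule of Events | x | | x | x | | x | x |
| Data collection section | x | x | x | x | x | x | x |
| Table 1 | x | | x | | | x | x |

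Table 1 stands alone in omitting 12 months. The data collection section stands alone in adding 3 and 15 months.

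**Step 3: what the 12-month wave is worth.** The protocol states no power or detectable effect for GDS 15 or GHQ-12, so there is no figure of its own to reproduce. What follows is illustrative.

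Inputs from the Sample Size section: 30 clusters, 15 per group; 10 per cluster less 20% attrition, so m = 8; ICC 0.05 (stated for the primary outcomes, borrowed here); power 0.80; alpha 0.05, taken as two-sided. Assumed, not in the document: correlation r between two measurements on the same person, 0.5 or 0.7.

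Model from the Data Analysis Plan: fixed time and intervention status, random cluster and individual, constant effect. With total variance 1:

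- cluster variance τ² = 0.05, person variance π² = r − 0.05, residual s² = 1 − r
- B = τ² + π²/m and W = s²/m
- x = difference in exposure between Group A and Group B at each of T waves
- information I = (15/2)(1/W)[Σx² − B(Σx)²/(W + TB)]
- detectable effect = 2.80/√I

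For r = 0.5: B = 0.05 + 0.45/8 = 0.10625 and W = 0.5/8 = 0.0625. For r = 0.7: B = 0.05 + 0.65/8 = 0.13125 and W = 0.3/8 = 0.0375.

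Year-1 contrast, x = (0,1) under Table 1 and (0,1,1) under the text. For r = 0.5:

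- Table 1: I = 120 × [1 − 0.10625/0.275] = 73.6, detectable effect 0.326 SD
- Text: I = 120 × [2 − 0.425/0.38125] = 106.2, detectable effect 0.272 SD
- Variance ratio 106.2/73.6 = 1.44

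Constant-effect model over all waves, x = (0,1,0,0) and (0,1,1,0,0). For r = 0.5:

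- Table 1: I = 120 × [1 − 0.10625/0.4875] = 93.8, detectable effect 0.289 SD
- Text: I = 120 × [2 − 0.425/0.59375] = 154.1, detectable effect 0.226 SD
- Variance ratio 154.1/93.8 = 1.64

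| Analysis | r | Table 1 (SD) | Text (SD) | Extra variance under Table 1 |
|---|---|---|---|---|
| Year-1 contrast | 0.5 | 0.326 | 0.272 | 44% |
| Year-1 contrast | 0.7 | 0.264 | 0.224 | 39% |
| Constant effect | 0.5 | 0.289 | 0.226 | 64% |
| Constant effect | 0.7 | 0.226 | 0.178 | 62% |

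In the constant-effect model, a comparison with 80% power under the text schedule would have about 59–60% under Table 1.

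**Step 4: sensitivity.** A wider grid was run for the constant-effect model: within-person share 0 to 0.7, ICC 0.01 to 0.10, cluster autocorrelation 0.8 or 1, and 8 or 10 per cluster. The variance ratio ranged from 1.61 to 1.90.

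**The case against.** The strongest reply is that nothing need be lost. Three text sections include 12 months, and one of them is the section that sets the schedule and says every participant follows it. The Outcomes section refers to Table 1 only for the list of instruments. On a plain reading the text governs and the table has two missing entries. This stands: the loss is conditional on Table 1 being followed.

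A reader might go further and infer that the wave will in fact be lost because sites will work from the table. The document does not support that. Data are collected by a blinded research officer at face-to-face visits, no section says that Table 1 is the working schedule, and the full protocol and data forms are not shown. Nor does anything suggest a deliberate decision to skip 12 months; no reason is given, and the text says the opposite.

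It is also fair to say that both outcomes are secondary, that the study is sized on QOL-AD and CES only, and that those two have entries at all seven waves. Even under Table 1 the 6-month comparison remains, and the mixed model also uses the 18- and 24-month data. The magnitudes rest on a borrowed ICC and an assumed within-person correlation.

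Finally, Figure 1 is not available here, so the 12-month visit's place before Group B's start is read from the year 1/year 2 wording. The reading is reasonable but is an inference.

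These points limit the severity. They do not remove the contradiction about which data are collected.

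**Conclusion.** The inconsistency is real and is wrong as written; it should be fixed. Following Table 1 would halve the post-baseline waves with concurrent usual care for GDS 15 and GHQ-12, from two (6 and 12 months) to one, and would leave no such comparison at the end of the 12-month intervention. The sizes in the working hold only in that case, on the stated ICC and attrition and the assumed correlations, and with month 12 falling before Group B starts. It would be too strong to say that the two hypotheses become untestable, or that the trial's main conclusions are at risk.

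**What to change.** Enter GDS 15 and GHQ-12 in the 12-month column of Table 1, to match the Outcomes section and the Schedule of Events. In the same correction, reword the data collection section so that primary measures are taken at all seven waves and secondary measures at baseline, 6, 12, 18 and 24 months, not at 3 and 15 months. It would help to state that the 12-month visit precedes Group B's start.

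The cost is a text and table correction before data collection. For participants, relative to Table 1, it means two short questionnaires at a 12-month visit that already takes place for QOL-AD, CES, RUD and the interviews.

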## Economic Methodology and Analysis

Utility measured by EQ-5D-5L (13)Reduction in health service utilization measured by RUD and administrative dataReduced carer time (paid and unpaid) measured by RUDDelay in permanent admission to residential care.

### Schedule of Events

At baseline, we will administer the primary and secondary measures to all participants. At 3, 6, 12, 15, 18, and 24 months, we will administer the primary measures. At 6, 12, 18, and 24 months, we also administer the secondary measures. All participants will follow this schedule of data collection regardless of group allocation. See Figure 1.

The intensive intervention phase at each cluster is shown in Figure 1. During this phase, the intervention will be actively promoted at the indicated clusters. The post-intervention phase is shown in light-blue, where participants can still access the intervention, but the intervention will no longer be actively promoted at those clusters.

### Sample Size

The study is powered to detect small–medium effects in the primary outcome measures of QOL-AD for people with dementia or cognitive impairment (0.23 effect size) and in the CES for carers (0.25 effect size).

The sample size required is 30 clusters with 10 participants/families in each to allow for an attrition of 20%. This is a total of 100 participant/families (50 in each group) in each of the 3 states, making a total sample size of 300. This will detect significant differences in caregiver’s and people with dementia or cognitive impairment’s quality of life between two groups at effect sizes of 0.23–0.25 (small–medium effects). Sample size calculations were completed using STATA statistical software stepped wedge: for clusters defined at the level of the community health center, power of 0.80, significance level set at 0.05, intraclass correlation coefficient (ICC) of 0.05, the number of steps (2), participant data collected at seven time points (baseline, 3, 6, 12, 15, 18, and 24 months), and primary outcome distributions as described in existing literature, i.e., QOL-AD scores between 15 and 60 and SD of 7 (6, 7, 14, 15) and CES scores between 0 and 100 and SD of 10 (8, 9).

### Recruitment

Participants with dementia or cognitive impairment and their carers/family members will be randomly assigned from community health center client lists and then randomly allocated to receive either the dementia “Support for Life” program (Group A, *n* = 50 per state) or routine care only (Group B, *n* = 50 per state).

We will apply quota sampling so that clusters comprise of essentially similar participants. Ten participants from each cluster are required, and so recruitment will cease within the following subgroups at each cluster when the following characteristics are attained:
–Age
○Five participants are aged <65 years○Five participants are aged >65 years–Gender
○Five females○Five males–Diversity/cultural background
○Eight born in Australia○Two from CALD/LGBTI communities

## Methods: Assignment of Interventions (For Controlled Trials)

### Randomization

Clusters are community health centers participating in the study. Randomization of clusters to an intervention year (1 or 2) will be done using a minimization routine balancing numbers in groups as randomization proceeds (16). To guard against confounding by major differences in clusters, randomization will be stratified by state (Victoria, New South Wales, or Queensland), area (metropolitan or regional), and socioeconomic status of area that cluster is located within [defined by 1–3 versus 4–5 quintile of the area index of relative disadvantage (IRSD)].

### Allocation

#### Sequence Generation

Participants with dementia or cognitive impairment and their carers/family members will be randomly selected from community health center client lists and then randomly selected to receive either the dementia “Support for Life” program (Group A, *n* = 50 per state) or routine care only (Group B, *n* = 50 per state).

#### Allocation Concealment Mechanism

Computer generated randomization of Group A and Group B will be performed by an independent researcher after the baseline data are collected.

#### Implementation

The allocation sequence will be developed by a statistician blinded to the study details. Identified potential participants will be approached, recruited, and enrolled by experienced members of the research team in each state. The statistician who generates the allocation sequence mentioned above will pass this code to the overseer of the recruitment process.

#### Blinding (Masking)

The Research Officer undertaking the data collection will be blinded to participant group allocation. Participants (people living with dementia or cognitive impairment in the community, carers of people with dementia or cognitive impairment living in the community, and family members of people with dementia or cognitive impairment living in the community) will be blinded to their group allocation.

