### Data Management

All hard copy and audio-recorded data will be kept confidential and stored in a locked filing cabinet in the research group office and in softcopy in a password protected database according to ethical storage and disposal of data as stated in the NHMRC guidelines. Data will be only accessible to the chief investigator research officer, project manager, and statistician. The research team will monitor the integrity of the trial data. All participant data will be entered into an appropriate database such as Redcap (https://projectredcap.org/) or the Statistical Package for Social Sciences (SPSS) package and screened to detect any errors. A range of checks will be undertaken prior to data analysis.

The project manager will be employed to oversee the project and to manage the project data from each of the three states, including data cleaning and data merging.

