### Statistical Methods

#### Data Analysis Plan

##### Quantitative Analysis

###### Primary Analyses

We will use all data along with the original designated group allocation and an intention to treat approach as the primary analytic framework. Descriptive data on both groups will be reported including demographics, stratification variables, baseline measures, and number of times intervention was accessed. Descriptive statistics will be used to summarize the characteristics of all participants including carers and family members. Deterioration of the primary outcome measure in individuals due to increasing dementia severity/aging and occurring over the 2-year data collection period will be explored using multivariate analyses (including factors: intervention status, age, and gender). If the dementia severity/aging factor is found to be significant, it will be included in the main models described below.

A linear mixed effects model will be used to compare the intervention and usual care periods for continuous outcomes and generalized linear mixed effects model for binary outcomes. The model will include intervention status and time as fixed effects and cluster site and individuals as random effects. Where appropriate, cluster and individual factors strongly correlated with the outcome will also be included as fixed effects in the model. These may include the stratification variables, e.g., socioeconomic status of area. The estimated intervention effect will be reported as the mean outcome difference for continuous outcomes and odds ratio for binary outcomes between intervention and control periods, assuming a constant treatment effect over time. The estimated intervention effects will be reported with 95% CIs and *p*-values. The analysis will investigate an interaction effect between intervention and time.

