### Confidentiality

Personal information about potential and enrolled participants will be collected and then de-identified prior to it being shared to ensure confidentiality of participants is maintained before, during, and after the trial. Only the project manager, research team, and dementia support worker will have access to the final trial dataset.

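### The declared assessor blind is not credible from month 6, because the data collector asks about services and activities at the visits that yield the primary scores

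*Protocol article*

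**What the plan says.** All references are to the protocol article.

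- **Blinding (Masking)** says "The Research Officer undertaking the data collection will be blinded to participant group allocation". No time limit and no masking procedure are attached. The same section says that participants "will be blinded to their group allocation".
- **Methods: Data Collection, Management, and Analysis** says of data collection: "This will involve a face to face visit with a researcher". Of the interviews it says "Interviews will take place during the face to face visit and will be audio-taped prior to transcription". Participants may fill in the questionnaires beforehand or during the visit, and a proxy may supply data when needed.
- **Outcomes** and **Table 1** include service use by RUD, social engagement, and "Increased attendance at social activities/services (staff/family/carer report/interviews").
- **Schedule of Events** places the primary measures at every visit and the secondary measures at baseline and months 6, 12, 18 and 24. Months 3 and 15 carry primary measures only.
- **Trial Design**, **Intervention** and **Randomization** make the community health center the randomized unit. The intervention is delivered by a support worker, with an assistant and volunteers who help people reach services and social activity. Group B centers get access in year 2, when Group A participants may still use it.

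**The concern.** The blind is stated as a fact, but the same person is scheduled to ask questions whose honest answers tend to reveal the arm. A Group A family asked which services it uses and what activities it attends has good reason to mention the support worker. It need not know its group label to do so, so the declared participant blind offers no protection here.

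Because the whole center shares one allocation, what is learned from one family applies to its neighbours.

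At stake is the randomized year-1 comparison of the two primary outcomes. A collector who knows the arm could influence how QOL-AD is supported during the visit and when a proxy is used, and could influence the coding of interview outcomes. For CES the documents suggest only a weaker route, through completion in the collector's presence. If the report repeats the blinding statement unqualified, readers will credit the trial with a protection it may not have had.

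**Working it through.** **No plan figure to reproduce.** The point is procedural and does not depend on the sample size, power or significance level. The check sets the sections side by side and then illustrates the center-level effect.

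**Step 1: is it the same person?** Blinding (Masking) describes the Research Officer as the one who collects the data. The data-collection section has a researcher make the visit, at which the interviews are also held. That these are the same person is an inference, though the natural one.

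**Step 2: which primary scores are exposed by this route?**

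| Visit | Service, activity and engagement questions? | Primary scores exposed? |
|---|---|---|
| Baseline | Yes | No: randomization follows baseline (Allocation Concealment Mechanism) |
| Month 3 | No | No |
| Month 6 | Yes | Where the questionnaire follows the interview |
| Month 12 | Yes | Yes: it follows the month-6 interviews at the same center |
| Months 15, 18, 24 | At 18 and 24 | Every center has access, so exposure to the intervention is known in any case |

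The opening of the data-collection section names primary and secondary data together for all time points. The table follows the more specific Schedule of Events and Table 1.

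**Step 3: how far does one disclosure reach?** Let p be the chance that a Group A family reveals support-worker contact in one interview round, and m the number of families whom the same researcher sees at the center. If families are independent,

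P(at least one disclosure) = 1 - (1 - p)^m.

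The Figure 1 caption gives 10 participants per center and 20% attrition, so m = 10, or 10 x 0.8 = 8. The documents do not give p; the values below are assumptions.

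| p (assumed) | m = 8 | m = 10 |
|---|---|---|
| 0.01 | 1 - 0.99^8 = 7.7% | 1 - 0.99^10 = 9.6% |
| 0.05 | 1 - 0.95^8 = 34% | 1 - 0.95^10 = 40% |
| 0.10 | 1 - 0.90^8 = 57% | 1 - 0.90^10 = 65% |
| 0.20 | 1 - 0.80^8 = 83% | 1 - 0.80^10 = 89% |

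The answer depends almost entirely on p.

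**Step 4: scale of the target.** Sample Size aims at 0.23 SD with SD 7 for QOL-AD (0.23 x 7 = 1.61 points) and 0.25 SD with SD 10 for CES (0.25 x 10 = 2.5 points). These are small differences. The documents give nothing from which to estimate a bias to set beside them.

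**The case against.** The strongest reply is that the documents show a blind at risk, not a procedure that breaks it. The Implementation section sends the allocation code to the overseer of recruitment, not to the Research Officer. Questionnaires may be completed before the visit, and scores obtained that way precede that visit's interview. A condensed article may also leave instrument order and database permissions to the full protocol. Much of this stands: failure is not certain, and the absence of those details is not itself the point. What remains is a conflict between two stated procedures. Completion before the visit is optional, so it protects only some participants.

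Several stronger readings are tempting, but the documents do not support them.

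- **Data access unblinds the assessor.** Data Management says "Data will be only accessible to the chief investigator research officer, project manager, and statistician", and Primary Analyses lists the "number of times intervention was accessed" among the descriptive data. But the first is ambiguous as punctuated, and neither says that allocation or contact counts are visible to data collectors during follow-up.
- **The support worker's access matters for blinding.** Confidentiality says "Only the project manager, research team, and dementia support worker will have access to the final trial dataset". Access to a final dataset cannot unblind visits already made, and the support worker is not the assessor. The differing lists in Data Management, Confidentiality and Access to Data should be reconciled as a separate wording matter.
- **No blinding is possible in year 2.** Blinding to intervention exposure is lost. But both groups can then use the intervention, so a mention of a support worker need not identify the original group.
- **One disclosure always reveals the whole center.** This requires one researcher to see all its families, which is not stated. It also requires center-level allocation. That is the design throughout, although Recruitment and Sequence Generation contain looser participant-level wording.
- **The higher disclosure rates are estimates, or a bias of known size follows.** No rate and no bias is documented.

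**Conclusion.** The concern holds in a limited form. The assessor blind cannot be relied on from month 6 under the stated procedure. In the year-1 comparison the exposed primary scores are those at month 12, and at month 6 where the interview came first. In year 2 the assessor cannot be blind to intervention exposure, although blinding to original group is not thereby impossible.

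The size is undetermined: the chance that a Group A center is revealed in one interview round runs from 8-10% to 83-89% as p goes from 0.01 to 0.20. That range assumes independent families and a single researcher per center. No bias in QOL-AD or CES can be calculated from the documents. The change is still worth making before the first month-6 visit, because it costs little and lost blinding cannot be restored afterwards.

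**What to change.** 1. At every visit, have QOL-AD and CES completed and closed before any RUD, activity or interview question, or completed before the visit as the article already allows. This protects the scores of that visit; it does not undo what was learned at an earlier one, so the remaining steps are also needed.
2. Keep intervention-contact data and interview transcripts from data collectors until their last visit. This is a precaution, since the documents do not show that they have such access.
3. Record the assessor's guess of allocation in year 1, so that the report can state how well the blind held.
4. Amend Blinding (Masking) to say that assessor blinding is attempted, may be lost from month 6, and does not cover intervention exposure in year 2.
5. Where a state already has more than one data collector, exchange them between centers after month 6. The article does not state the staffing, so this should not be a general requirement.

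Steps 1 to 4 cost protocol wording, database permissions and one form item. Step 5 costs some travel and some loss of rapport with families.
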